**Fig. 2 Fig2:**
[figure not shown]
Results of the sample size calculations

#### Inclusion and exclusion criteria

To be eligible (Table 2), facilities and units have to participate in the TREC observational study, as *INFORM* outcomes are only available for these facilities. We will only include facilities and units located in Alberta or British Columbia, as the TREC Manitoba facilities are participating in another TREC intervention study. Facilities need to have at least one unit with ten or more care aide responses on the TREC survey used to assess organizational context and staff outcomes. Only care units with ten or more care aide responses on the baseline TREC survey are eligible. From our previous work [115] we know, this number is required to ensure stable, valid and reliable aggregation of the study outcomes at the unit-level. From our observational study we know, there are two facilities for which we cannot assign HCA surveys to the microsystem. We excluded them as unit-level analyses are not possible for those facilities. We will only include units with an identifiable care manager or leader accountable.

**Table 2 Tab2:** Inclusion and exclusion criteria for facilities and units

	Inclusion criteria	Exclusion criteria
Facilities	• Participation in the TREC observational study • Located in one of four health regions in Alberta (Edmonton or Calgary) or British Columbia (Fraser Health or Interior Health) • Have at least one care unit with ten or more care aide responses to our survey that we use to assess organizational context and staff outcomes at baseline (T_-2_)	• Does not participate in the TREC observational study • Located in the Winnipeg Regional Health Authority • Do not have at least one care unit with ten or more care aide responses to our survey that we use to assess organizational context and staff outcomes • Surveys collected in this facility cannot be assigned to a clinical microsystem as defined by TREC within this facility
Care units	• Located within a facility participating in the TREC observational study in Alberta or British Columbia • Ten or more care aide responses to our survey that we use to assess organizational context and staff outcomes are available • A care manager can be identified who leads this unit	• Not located within a facility participating in the TREC observational study in Alberta or British Columbia • Less than ten care aide responses to our survey that we use to assess organizational context and staff outcomes are available • No care manager can be identified who leads this unit

Based on these criteria, 203 units in 67 facilities are potentially eligible.

#### Enrolment, randomization, allocation

An independent person, not otherwise involved in this study, randomly assigned the 67 facilities to each of the three study arms. Randomization was stratified by health region (Edmonton, Calgary, Fraser Health, Interior Health) to account for the different policies within those regions that might influence organizational context and quality of care, and to facilitate delivery of the feedback intervention. We maintained regional proportionality of the 67 facilities within each study arm. From the list of facilities in each of the four regions, we selected the required number of facilities to be assigned to each of the three study arms by assigning a computer-generated random number to each facility. To facilities assigned to BAF or EAF we will offer *additional feedback*. We will explain to managers the specific extra feedback (treatment) they will receive, but we will blind them to group allocation.

#### Prevention of contamination

To limit the possibility of contamination, we will perform a cluster randomization. While we cannot prevent managers from talking to each other at regional or provincial meetings, contamination is less likely when study units are physically separate, interventions are more complex, and/or aim at changing behavior [116, 117]. We will also enlist participants’ agreement *a priori* to not share workshop tools with other managers or facilities during the study. The *INFORM* intervention is a complex intervention involving professionally facilitated face-to-face and virtual interaction with guided goal setting. It is therefore unlikely that managers in SF sites would be able to implement such an intervention unaided [118] or to change practice by virtue of interaction with intervention site managers at professional and other similar meetings. While we cannot fully blind all participants to all aspects of the study, we have undertaken comprehensive efforts to blind different stakeholder groups involved in INFORM as best as possible (details Additional file 6).

### Outcomes and instruments

Additional file 7 contains a summary table listing study outcomes, tools used to assess these outcomes, and their psychometric properties. Our outcome definition includes the name of the outcome, the time point each outcome will be assessed, the method of aggregation, the metric (e.g., change from baseline or group differences at a given time), the definition of the concept assessed, psychometric properties and an example item of each scale used.

#### Primary outcome

Based on arguments outlined in Additional file 5, we selected the ACT FI score as the primary outcome. FI is defined as “formal exchanges that occur between individuals working within an organization (unit) through scheduled activities that can promote the transfer of knowledge” [80]. The FI scale consists of four items asking care aides how often, in the last typical month, they participated in (a) team meetings about residents, (b) family conferences, (c) change-of-shift report, and (d) continuing education (conferences, courses) outside the nursing home (rated from 1 = never to 5 = almost always). The overall score is generated by recoding each item (1 and 2 to 0; 3 to 0.5; 4 and 5 to 1) and summing recoded values (possible range: 0–4).

#### Secondary outcomes

##### Organizational

We will assess three additional organizational context factors (evaluation, social capital, slack time) using the ACT, which is embedded within the TREC care aide survey, a suite of validated survey instruments completed by computer-assisted personal interview. We will also capture response to major near misses and managers’ organizational citizenship behavior, using data from our TREC unit survey, and performance reports and quality improvement activities, using data from our TREC facility survey. These instruments are described elsewhere [48, 49, 80, 102, 119].

##### Staff

We will capture instrumental and conceptual best practice use, psychological empowerment, job satisfaction, and a number of individual staff attributes, using the TREC care aide survey.

##### Residents

We will obtain resident data from the RAI-MDS 2.0, which is used internationally for comprehensive geriatric assessment of the health, physical, mental, and functional status of nursing home residents [61]. In Canada its use is mandated in several provinces/territories, as well as by the Canadian Institute of Health Information for national reporting [120]. Data for calculating QIs are captured in quarterly assessments completed on all residents [121]. The two practice sensitive (i.e., modifiable by care staff) QIs [122] worsening pain and declining behavioural symptoms will form the focus at unit and facility levels.

#### Process measures

##### Evaluation of the intervention sessions

We will adapt previously used questionnaires to the needs of this study. These surveys will include closed and open ended questions relating to participants’ intention to change, satisfaction with intervention components and with the intervention overall. These evaluation forms will be completed by participants at the end of the Goal Setting Workshops for both the BAF and the EAF arms, and at the end of the two support workshops; virtual for the BAF arm and face-to-face for the EAF arm.

##### Evaluation of intervention fidelity

To ensure that each intervention session is delivered as planned, consistently across arms and time, staff will work from study protocols. To evaluate protocol fidelity, study staff will observe, using a protocol checklist, adherence to workshop protocols during actual workshop delivery. There will also be space for staff to record field notes during each intervention session. We will track (a) how many of the participants invited to the workshops attended the workshops, (b) how many of the participants attended the workshop the full time, and (c) how many of the participants completed the workshop evaluations. For consistency of workshop delivery, the same facilitator and researcher will be present in all workshops. The regional lead will change for each region, but will be consistent across workshops within one region. For consistency of evaluation, the same staff member will complete field notes and fidelity checklist across workshops. This person will also run workshop debriefing sessions with the facilitator and researcher-regional decision maker dyad.

##### Evaluation of processes in the facilities

We will evaluate with the BAF and EAF managerial care teams: (1) to what extent they achieved the quality improvement goals defined in the workshops, (2) if they were able to apply the planned strategies in practice, (3) barriers and facilitators encountered, and (4) strategies applied to overcome challenges. We will conduct the evaluations as follows:Detailed documentation of the first support workshop: We will document discussions and results in the first support workshop around the above named topics using detailed field notes, and we will analyze them using qualitative content analysis.Focus Group 1: We will hold the first focus group one month following the second support workshop for BAF and EAF arms. The second support workshop is the final intervention component to which the participants are exposed. This will provide participants with the opportunity to reflect on the entire INFORM Intervention. We will ask participants in each region to sign up for a teleconference focus group session held at varying times to meet the needs of individual schedules (held separately for BAF and EAF groups).Focus Group 2: We will hold the second focus group (organized the same way as the first focus group) one month before the long-term follow up data collection for both intervention arms. This will enable the research team to assess sustainability of the INFORM Interventions.

We will also conduct semi-structured interviews with SF care unit managers. We will ask questions about: people’s understanding of the ACT data, changes made on their unit as a result of feedback they received during the Fall 2015 TREC dissemination meetings, and barriers/facilitators to change. These interviews will allow us to compare the three study arms in terms of their ability to use the ACT data to improve context – the ultimate aim of INFORM. SF interviews will also provide information on additional quality improvement activities outside of INFORM, which may have contributed to unexpected “context” improvement during the intervention period.

##### Cost assessment

We will assess costs for *delivering* the INFORM interventions. We will not include costs related to *developing* the interventions and to *assessing the effectiveness* of the interventions (i.e., research costs). Using these data, we will assess and compare intervention delivery costs for the three study arms. We will collect data on all direct salary (workshop facilitator) and non-salary operating and travel expenses from University of Alberta accounting software, itemized by subcategory. The facilitator and study staff will keep detailed records of time invested in preparing and delivering each intervention. The cost of time invested by regional investigators and decision makers will be included. We will ask care unit managers monthly how much additional time and costs they and their staff spent on INFORM activities (i.e., not related to regular care or quality improvement activities), using standardized questions.

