Semi-structured interviews with *SF* unit managers					X (01/2017)			
Basic cost evaluation of the intervention				–––––––	–––––––	–––––––		

*BAF* Basic Assisted Feedback; *EAF* Enhanced Assisted Feedback; *SF* Standard Feedback

INFORM is set in urban nursing homes participating in our current phase of TREC – a stratified (region by size by operator) random sample of 91 urban sites. We recruited these sites recruited from three provinces: Alberta, British Columbia, Manitoba. These TREC facilities participate in a longitudinal observational study that generates a rich set of resident, staff, unit, and facility level measures and outcomes. Data from this ongoing observational study forms the baseline assessment, and data from future waves of this study will form the post-intervention and long-term follow-up assessments. We will invite all eligible sites in Alberta and British Columbia to participate in INFORM (sample information sheet and informed consent, Additional file 3). TREC Manitoba facilities are not eligible to INFORM, as they are participating in another TREC intervention study.

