We assumed that the FI score will increase by β_1_ = 0.2 in the SF group, by β_2_ = 0.4 in the BAF group, and by β_3_ = 0.6 in the EAF group. Based on these simulations (Fig. 2) 12 facilities per study arm (on average 3 units per facility) are required to detect the assumed effects with a statistical power of 0.90. To allow for attrition and effects smaller than the assumed ones, we will invite all eligible units in the 67 eligible facilities (see below) in Alberta and British Columbia for participation.

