## Discussion

INFORM is the first study to systematically assess effectiveness of different strategies to feed back research-based performance data to nursing home care units in order to improve their performance. In TREC we collect comprehensive longitudinal data on nursing home and care unit structural characteristics; modifiable features of nursing home and care unit work contexts; care providers’ use of best practices, health and quality of worklife; and various resident outcomes based on the RAI-MDS 2.0. Systematic feedback of these research data has been an important part of the long term TREC program. With INFORM we will be able to not only feed back data, but to systematically and comprehensively assess the most effective and cost-effective way to do so.

Our feedback interventions are based systematically on theory and evidence related to audit and feedback in the health care and organizational literature, goal setting, complex adaptive systems, and our own experiences with feeding back research results. This addresses Ivers and colleagues’ urgent call for systematic use of theory in future audit and feedback studies [129–131]. Furthermore, in order to determine which approaches to audit and feedback are most likely to change behaviours and improve performance, and to understand why these approaches work, head-to-head comparisons of different audit and feedback approaches, rather than comparison of audit and feedback with no intervention, are needed [129, 130].

We hypothesize that BAF and EAF will be significantly more effective than SF in improving formal interactions, context overall, and care provider as well as resident outcomes on nursing home care units. We furthermore expect that BAF and EAF will be similarly effective in doing so. However, we expect BAF to be more cost-effective than EAF. Results of this study will enable us to develop a practical, sustainable, effective, and cost-effective assisted feedback strategy that managers and policy makers can routinely use to improve performance of nursing home care units.

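### The article promises a verdict on cost-effectiveness, but its only stated economic analysis compares delivery costs and never relates them to the effect on formal interactions

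*Protocol article*

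**What the plan says.** The Cost assessment section of the protocol article, placed under Process measures, sets the scope: "We will assess costs for *delivering* the INFORM interventions". Development and research costs are left out. Facilitator salary, operating and travel expenses, the time of regional investigators and decision makers, and the extra time and costs reported monthly by care unit managers are counted. One analysis of these data follows: "Using these data, we will assess and compare intervention delivery costs for the three study arms". Table 1 in the Design section calls the work "Basic cost evaluation of the intervention". The Statistical analysis section does not mention costs.

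The Discussion goes further. The trial will "systematically and comprehensively assess the most effective and cost-effective way to do so", and "we expect BAF to be more cost-effective than EAF". The sentence before that expectation reads: "We furthermore expect that BAF and EAF will be similarly effective in doing so". The abstract also lists a cost-effective strategy among the trial's products. The sample size section, by contrast, assumes that FI rises "by β_2_ = 0.4 in the BAF group, and by β_3_ = 0.6 in the EAF group".

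**The concern.** Cost-effectiveness is a statement about cost and effect together. The article estimates the effect on FI in one place and compares delivery costs in another, and does not say how the two will be combined. This is more than detail left to a fuller plan, because the Cost assessment section says which analysis will be done, and that analysis answers a narrower question than the Discussion poses.

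The cost comparison between BAF and EAF is also largely settled by design. If the more intensive arm costs more, as is very likely, that result says nothing about whether its extra cost buys extra FI. BAF could then be recommended as cost-effective mainly because it is cheaper. A strategy for routine use that is cost-effective as well as effective is one of the trial's stated products, so the basis for that word should be fixed before the results are known.

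**Working it through.** **1. Claim against analysis.** The claim (Abstract and Discussion) is which strategy is cost-effective, with BAF expected to beat EAF. The analysis (Cost assessment; Table 1) is delivery cost by arm. The effect (Primary analysis) is a mixed-effects model for FI by arm. No section gives a ratio of cost to effect, a value for an FI point, or a rule for reading cost and effect together.

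**2. Direction of the cost difference.** Both arms have a face-to-face Goal Setting Workshop. The first support workshop is a 90-minute webinar in BAF and a 180-minute session at a conference venue in EAF. The second is described as similar in content. If it has the same length (an assumption), support time is 2 × 90 = 180 minutes in BAF and 2 × 180 = 360 minutes in EAF. EAF also has e-mail and phone support throughout. EAF very probably costs more.

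**3. What costs alone can settle.** Let the costs be C_B < C_E and the FI gains E_B and E_E.
- If E_B ≥ E_E, BAF dominates and the cost comparison suffices.
- If the gains are shown to be equivalent within a margin, cost-minimisation applies and the cost comparison again suffices.
- If E_E > E_B, neither arm dominates. The ranking needs (C_E − C_B)/(E_E − E_B) and a judgement of what an FI point is worth.

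**4. Where the plan's own figures fall.** The sample size section assumes gains of 0.2 (SF), 0.4 (BAF) and 0.6 (EAF), each against no feedback. So E_E − E_B = 0.6 − 0.4 = 0.2, which is the third case.
- Average cost per FI point, against no feedback: BAF is better if C_B/0.4 < C_E/0.6, that is, if C_E/C_B > 0.6/0.4 = 1.5.
- Against SF, the gains are 0.4 − 0.2 = 0.2 (BAF) and 0.6 − 0.2 = 0.4 (EAF). BAF is better if EAF's extra cost over SF exceeds 0.4/0.2 = 2 times BAF's.

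The answer depends on the size of the cost ratio and on the comparator, not just on which arm is cheaper. No cost figures are given, so it cannot be taken further.

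**5. Side check: could similar effectiveness be shown?** Inputs are the article's SDs (facility 0.154, unit 0.104, residual 0.192) and 3 units per facility. Assumptions are one baseline and one post-intervention wave, a baseline mean shared by the arms, a normal approximation and two-sided alpha 0.05.
- Variance of a facility mean at one wave: 0.154² + (0.104² + 0.192²)/3 = 0.0396.
- Covariance between waves: 0.154² + 0.104²/3 = 0.0273.
- Baseline-adjusted variance: 0.0396 − 0.0273²/0.0396 = 0.0208 (unrounded inputs).
- Check against the plan: with 12 facilities per arm, SE = √(2 × 0.0208/12) = 0.0588 and power for a difference of 0.2 is 0.925, close to the stated 0.90.
- With 67/3 = 22.3 facilities per arm, SE = √(2 × 0.0208/22.3) = 0.0431. The 95% half-width is 0.0431 times 1.96 to 2.00, or 0.084 to 0.086. The 90% half-width, as used in two one-sided equivalence tests, is 1.645 × 0.0431 = 0.071.

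A margin below about 0.07 FI points could therefore not be met even if the observed difference were zero. A true EAF advantage of 0.05 would reach significance only about 21% of the time, and one of 0.08 about 46%. A non-significant BAF–EAF difference is thus not evidence of similar effect. These figures describe the precision of the effect, not an error in the costs.

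**The case against.** The strongest reply is that the article's reasoning is cost-minimisation. It expects BAF and EAF to be similarly effective, and then a delivery-cost comparison is the right input. FI effects and delivery costs are both collected by arm, so a joint reading needs no new data. The cost work is a process measure, labelled basic; cost-effectiveness is not among the listed aims or the primary and secondary outcomes.

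Much of this stands, and it rules out several stronger readings:
- A reader might infer that no cost-effectiveness conclusion can be drawn. The documents do not support that: the conclusion follows if the cheaper arm is at least as effective or is shown to be equivalent.
- A reader might infer that an EAF advantage would count for nothing. FI is the primary outcome, so its contrast would be available beside the costs.
- A reader might infer from Table 1 that Standard Feedback's cost is lost, because the cost row covers 05/16 to 05/17 and the Dissemination Workshops were held in 10/15 to 11/15. All arms received those workshops, so their cost cancels from incremental contrasts, and the expenses may be recoverable from the accounting records.

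What the reply does not remove is that similar effectiveness is an expectation without a margin or test, and that the sample size section assumes the opposite.

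**Conclusion.** The point holds in a limited form. The article states a cost-effectiveness conclusion, and the only economic analysis it states is a comparison of delivery costs. That analysis supports the conclusion for BAF against EAF only if BAF is shown to be at least as effective or equivalent. The article gives no equivalence margin, and its own design assumption puts EAF 0.2 FI points ahead. Under that assumption the ranking by average cost per FI point turns on whether EAF costs more or less than 1.5 times BAF.

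This rests on EAF costing more than BAF, which is very probable from the workshop format but is not documented in figures. The consequence for a recommendation cannot be quantified without cost data. The change is worth making because it is cheap and the claim is prominent; the primary FI analysis does not depend on it.

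**What to change.** In the Cost assessment section, choose one of three options.
- **Joint analysis.** Add the incremental delivery cost per FI point gained, for BAF against SF and EAF against BAF. Use arm-level delivery costs and the FI contrasts with confidence intervals from the primary mixed model. Handle cost uncertainty by sensitivity analysis. Goal Setting Workshops are held by region and arm, so resampling facilities over apportioned workshop costs would give largely artificial cost uncertainty.
- **Cost-minimisation.** Make the cost comparison conditional on equivalence of BAF and EAF within a prespecified FI margin, and reconcile this with the 0.2 step in the sample size section.
- **Narrower claim.** In the abstract and the Discussion, replace cost-effectiveness with delivery cost.

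If total cost per arm is reported, include the 10/15 to 11/15 Dissemination Workshop costs.

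The cost is a change of wording and a modest analysis of data already planned or on record. The incremental ratio still needs a value judgement about the worth of an FI point, which the article does not give; the text should say so.
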